**7.4 Study activities at subsequent routine antenatal visits**

*7.4.1 Clinical data collection*

At each subsequent scheduled antenatal visit, information will be collected from the participant on any treatments sought since the previous visit and on current symptoms, and a brief clinical assessment will be performed by a health center staff clinician.

*7.4.2 Laboratory sample collection*

Study staff will collect blood from participants for use in study laboratory procedures, and will prepare the samples and conduct the diagnostic tests described; all other care will be provided by health center staff (i.e. clinicians, typically midwives and nurses, employed by the health center). At each scheduled visit, the participant will provide a 2 mL (two milliliter) venous blood sample for HemoCue Hb measurement, preparation of two RDTs, preparation of thick and thin smears for light microscopy, and storage in a microtainer and on filter paper for PCR (see further details in section 7.6 below). Hb and RDT results will be used in clinical management as in sections 7.4.3 and 7.6.1 below; microscopy and PCR results will not be immediately available and will not be used in management.

*7.4.3 Administration of antimalarial medicines*

If both RDT results are negative, the participant will receive a complete dose of SP by DOT. If one or both RDTs are positive, she will receive a complete curative dose of ACT or quinine (as in section 7.3.3 above); the initial dose will be given by DOT, and the remaining doses will be given to the participant with clear instructions for completing the regimen at home. SP or ACT/quinine will be administered by health center clinical staff. If a patient receives curative treatment with ACT or quinine, a return visit (or home visit by study staff) to administer a dose of SP will be scheduled for 2 weeks after the end of the curative treatment. (See section 7.3.3 for explanation of rationale.)

*7.4.4 Provision of symptomatic and routine antenatal care*

Any symptoms reported by the participant at the visit will be investigated and managed according to the local standard of care by the health center staff clinician providing care, as described in section 7.3.4. Data will be collected on symptoms reported and any treatments given, and information on provision and use of routine antenatal care will be recorded. If, in the judgment of the health center staff, a participant requires referral for medical reasons, this will be done according to usual health center procedures as in section 7.3.4.

**7.5 Study activities at the time of delivery**

At delivery, study staff will collect a 2 mL (two milliliter) blood sample from the participating mother by venipuncture, and from the placenta by standard methods. Maternal peripheral blood will be measured for Hb by Hemocue; both maternal and placental blood will be used to prepare RDTs and blood smears, and for storage in microtainers and on filter paper for PCR (see further details in section 7.6). In addition, placental tissue samples will be processed for histopathological examination using standardized methods. Infant birth weight will be obtained using a calibrated scale. If a participant does not deliver at the study site, study staff will attempt to visit her to obtain data and samples within 24 hours of the birth. Data on date, time and type of birth, any complications, maternal Hb and infant weight, and the date and time of collection of blood and placental samples and outcome data will be recorded.

Testing of mothers for malaria at delivery is not routine, and there is not yet an established standard of care for management of babies born to women testing positive under these circumstances. Congenital malaria remains a poorly understood occurrence.51, 52 However, some evidence suggests that risk of congenital malaria is higher for infants of HIV-positive women53 (note that this study will not enroll HIV-positive women), and for infants of primigravidae.54 Notably, an association between placental infection and clinical malaria in the infant is not yet well established.54 For this study, if maternal peripheral blood or placental blood is positive at delivery by RDT, study staff will inform the managing clinician and the mother of the result, and will recommend that the infant be observed for symptoms; if symptoms occur, the infant should be tested (if possible according to local standards of care) and treated for malaria according to national guidelines. In addition, when microscopy results become available, if maternal peripheral or placental blood smears are positive, study staff will notify the mother by phone or home visit. As on previous study visits, if in the judgment of health center clinical staff a participating mother or her infant requires referral for medical reasons, this will be done according to usual health center procedures as in section 7.3.4.

It is recognized that poor birth outcomes may lead to negative and stressful emotions for the woman, those close to her, and her health care providers. In the unfortunate event of a negative birth outcome, study staff will attempt to collect relevant data in a manner that is sensitive, respectful of the woman’s dignity, context-appropriate, and that presents the least inconvenience possible to the woman and her family. Discussion of these ideas, potential scenarios and appropriate methods will be held with study staff and health center staff during pre-study training, and will be based on existing guidance to the extent available.55, 56

**7.6 Specific clinical and laboratory assessments**

*7.6.1 Measurement of hemoglobin (Hb) and assessment of anemia*

At the time of each routine antenatal visit, and again at delivery, maternal blood will be used to measure hemoglobin with a HemoCue machine (Quest Diagnostics, Ängelholm, Sweden). Based on WHO definitions, a participant with Hb < 11 g/dL will be considered to be anemic, and Hb < 7 g/dL will be considered to be severe anemia. Anemia will be managed by health center clinical staff according to national guidelines for anemia in pregnancy, which may include additional iron and/or folate supplementation, and/or administration of an anti-helminthic. Data on provision of such care will be recorded (as in section 7.4 above).

*7.6.2 Rapid diagnostic tests (RDTs)*

This study will evaluate the three most commonly used antigen-detection systems in RDTs: *Plasmodium falciparum-*specific plasmodium lactate dehydrogenase (Pf-pLDH), pan-specific plasmodium lactate dehydrogenase (pan-pLDH), and histidine-rich protein 2 (HRP2). According to current test format availability, in order to obtain reliable results for HRP2, pan-pLDH and Pf-pLDH or this study, two different combination RDTs (i.e. each with two test lines detecting different antigens) will be used. RDTs will be obtained directly from their manufacturers, and will be centrally procured. For each of the two types of RDT to be evaluated, all test kits used in the study will be from a single lot. Batch numbers, expiry dates, date received, and date opened will be recorded for each package of RDTs. All study personnel will receive hands-on training in preparation and interpretation of the RDTs before the study begins.

*7.6.2.1 Quality control and storage of RDTs*

Each lot of RDTs will undergo lot testing according to WHO guidelines57 before and at the end of the study. RDT testing will take place in the laboratory of [name] at the Centers for Disease Control and Prevention (CDC), Atlanta, Georgia, USA. Prior to the start of the study activities at each site, the RDTs to be evaluated will be stored in their original packaging at room temperature in a central storage space. Stocks of RDTs, adequate to complete training and the study at each site, will be transported to each health center prior to the training and pilot period at each site. Manufacturers recommend that RDTs be stored between 4 and 40° C. Temperature and humidity of the storage areas will not be controlled, but will be monitored and recorded regularly to document storage conditions at each site.

*7.6.2.2 RDTs to be evaluated*

The following criteria will be considered in selecting the RDTs for this evaluation: high performance in WHO/FIND standardized product testing,27 ease of use, safety (minimal exposure to blood during test preparation), completeness of packaging, appropriate packaging for transport and storage in tropical environments (each test individually wrapped in foil with plastic liner), reasonable market price, and reliability of the supply of the RDTs.

*7.6.2.3 Preparation of RDTs*

RDTs will be performed on maternal blood obtained by venipuncture at the time of each routine antenatal visit, and at the time of delivery. In addition, RDTs will be performed on placental blood obtained at delivery. Individual RDTs will be labeled with the participant’s unique study number and initials. A member of the study staff will prepare the RDTs according to manufacturer instructions. All personnel will use universal precautions when handling blood samples.

*7.6.2.4 Interpretation and recording of RDT results*

Each RDT will be interpreted by study personnel who are not responsible for clinical management decisions. At the end of the manufacturer-recommended development time for each test (typically 15 minutes), the RDT result will be recorded on the patient’s data form and will be given to the clinician caring for the participant. An RDT result will be considered positive if both the control line and the test line are visible after the development time. A result will be considered negative if the control line is visible, but no test line appears. The result will be considered invalid if no control line is visible, regardless of whether or not a test line appears. If an RDT result is invalid, the test will be repeated using the same sample of venous blood.

*7.6.3 Microscopy*

*7.6.3.1 Preparation and reading of blood smears*

At the time blood is obtained for preparation of RDTs, at each routine antenatal visit and at delivery, a thick and thin blood smear also will be prepared. In addition, at the time of delivery, an impression smear will be prepared from placental blood according to standardized methods. Blood smears will be stained with Giemsa, fixed, and transported to a central laboratory at each participating site for expert reading. Microscopists reading blood smears will be blinded to the RDT results. Thick blood smears will be evaluated for the presence of parasitemia (asexual forms) and gametocytes. Parasite densities are calculated by counting the number of asexual parasites per 200 leukocytes (or per 500, if the count is <10 asexual parasites/200 leukocytes), assuming a leukocyte count of 8,000/l. A blood smear will be considered negative when the examination of 100 high power fields does not reveal asexual parasites or gametocytes. If a thick smear is positive, the corresponding thin blood smear will be evaluated for parasite species.

*7.6.3.2 Quality control of microscopy results*

Before the commencement of field work, designated microscopists at each site will be pre-qualified through blinded readings on slides prepared according to the WHO slide bank protocol, and required to reach level 1 or 2 expertise level (as described in the WHO Malaria Microscopy Quality Assurance Manual, version 1, Chapter 5).58 All slides collected during the study at each site will be read by two microscopists. Slides with discrepant results will be re-read by a third external reader (Level 1 WHO microscopist) and returned to the study site after reading. In addition, 10% of slides from each site will be sent for review at an internationally recognized center of excellence for malaria microscopy. All microscopists will be blinded to RDT results and to results of previous microscopy.

*7.6.4 PCR for detection and speciation of parasitemia*

As for RDT and blood smear preparation, at the time of each routine antenatal visit and at delivery, two drops of maternal blood will be collected onto filter paper and 250uL into a microtainer containing EDTA anticoagulant. In addition, at the time of delivery, placental blood will be collected onto filter paper and into EDTA microtainer/s. Each filter paper sample will be labeled with the participant’s study number, air-dried, and stored in a sealed plastic bag at ambient temperature. Microtainers will be labeled with the participant’s study number and stored at -20°C. Samples will be transferred to a central laboratory and analyzed by PCR to confirm presence or absence of parasitemia, and parasite species. PCR will be performed at the laboratory of [name] in Bobo-Dioulasso, Burkina Faso, and quality assurance of results will be conducted at the laboratory of [name] at the Centers for Disease Control and Prevention, Atlanta, Georgia, USA.

*7.6.5 Estimation of gestational age*

At enrollment, duration of gestation and expected delivery date will be estimated by reported last menstrual period (LMP) and by measurement of fundal height, and these data will be recorded on the participant’s case record forms. At subsequent study visits, fundal height will be measured and recorded.

*7.6.6 Measurement of infant birth weight*

Within 24 hours of delivery, study staff will weigh the infant on a calibrated scale. Birth weight will be recorded in grams; based on WHO definitions, low birth weight (LBW) will be considered < 2500 g.

*7.6.7 Placental histopathology for detection of evidence of prior or current placental malaria*

At the time of delivery, placental blood and tissue sample/s will be collected and processed according to standard methods for smears, storage for molecular analysis, and for histopathological examination. Specific details of placental collection will be described in more detail in site-specific protocols; in general, for births taking place at the health center, health center staff will assist with delivery, including delivery of the placenta, and will then work with study staff to ensure the placenta is transferred to the laboratory area for processing as efficiently as possible to avoid degradation of the samples. As in section 7.5, if a participant does not deliver at the study site, study staff will attempt to visit her to obtain data and samples within 24 hours of the birth. The placenta will be wiped and washed with approximately one liter of phosphate buffered solution (PBS) to remove blood clots, placed umbilical cord side down on a clean, dry cloth, and gently blotted with a paper towel. Placental blood samples and biopsies will be collected and stored for further staining and processing. Placental histology samples will be read by two expert microscopists with discrepant results resolved by a third reader, with a proportion of samples sent to an independent research group for external quality control.

*7.6.8 Collection of data on other maternal and fetal outcomes*

In addition to the specific assessments described above, data on other significant maternal and fetal outcomes will be collected. In particular, the study staff will endeavor to collect data on management of any febrile or afebrile illnesses during pregnancy, and on birth outcomes including requirement and rationale for Cesarean section, any obstetrical complications, and fetal or maternal death. If a participant does not return to the health center at the anticipated time of delivery, study staff will contact the participant by phone and/or conduct a home visit to attempt follow-up. A participant will be considered lost to follow-up if no data can be collected within 7 days of delivery; within the 7-day limit, complete or partial data (e.g. maternal blood and infant weight, but no placenta) may be collected.

**8 SAFETY CONSIDERATIONS**

## 8.1 Potential risks

Risks associated with participation in this evaluation are minimal, essentially no greater than they would be for routine antenatal care in malaria-endemic areas. All participants will receive standard-of-care antenatal services, including provision of IPTp with SP according to WHO and national recommendations. To the routine evaluation of pregnant women at antenatal visits, this study adds the collection of 2 mL (two milliliters) of venous blood, a negligible medical risk. Physical discomfort, transient bleeding and bruising may result when blood is obtained by venipuncture. Aseptic technique and universal precautions against body fluid exposures will be practiced in obtaining blood samples. Some participants will present to the health facility with asymptomatic or symptomatic malaria infection, which is potentially detrimental to both mother and fetus; however, all participants will be managed by qualified clinical staff according to WHO and national standards of care. While loss of privacy is a potential risk associated with participation in any research project, no sensitive information will be collected, and no social risks are foreseen for participating women. Potential for loss of confidentiality will be minimized by use of coded study numbers on data collection forms and laboratory samples, rather than participant names, and all data will be stored in locked filing cabinets and password-protected computer files.

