**Follow up at delivery**

- Maternal peripheral blood for Hb, RDTs, smear, and PCR
- Placental blood for RDTs, smear, and PCR
- Placental tissue sample to process for histopathological examination
- Measurement of infant birth weight
- (Other data on any maternal or fetal morbidity/mortality)

1. **STUDY POPULATION**

Participants in this evaluation will include pregnant women presenting for routine antenatal services in areas of Africa where IPTp is considered standard of care according to WHO and national malaria control program guidelines. Pregnant women of any parity will be eligible for enrollment. Anticipated sites include antenatal clinics in Burkina Faso, Nigeria, and Uganda. Specific participant selection criteria will include (please see also section 7.2 on participant enrollment):

1. Presenting for care after quickening and before onset of labor (i.e. in the second or third trimester of pregnancy)
2. Age between 16 years and 44 years, inclusive
3. Willingness and ability to follow up with study visits and activities through the duration of pregnancy and at delivery
4. Absence of history of serious adverse reaction to sulfa drugs
5. Absence of history of serious adverse reaction to artemisinin-based drugs or quinine (depending on national policy on treatment of malaria in pregnancy)
6. Absence of HIV infection (both because guidelines for malaria prevention in pregnancy for HIV-infected women differ from those for HIV-negative women, and in order to avoid confounding of pregnancy outcomes by HIV-related complications or treatments in this early evaluation)
7. Absence of history of or current obstetrical complications (e.g. pre-eclampsia, eclampsia, hypertension during pregnancy, post-partum hemorrhage, evidence of multiple gestation)
8. Absence of chronic disease (e.g. diabetes mellitus, sickle cell disease)
9. Absence of evidence of severe acute disease requiring inpatient management or referral
10. Provision of written informed consent
11. Enrollment Hb ≥7 g/dL

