**7.2 Study enrollment**

*7.2.1 Selection for recruitment and enrollment*

At each site, pregnant women will be invited to enroll in the study when they present to the participating health center for routine antenatal care. At each site, potential participants will be referred by health center staff to study staff, and will be screened and enrolled by study staff according to the selection criteria listed in section 6. At each participating site, information on current health status, obstetric history, and chronic conditions including HIV infection (see selection criteria 6-9 in section 6 above) are collected by health center staff as part of routine antenatal care. HIV counseling and testing is routinely offered to all pregnant women on an opt-out basis at each site. Study staff will conduct screening interviews with each potential participant after she has completed her antenatal visit for that day. Study staff will rely on health center staff’s diagnosis of these conditions in determining whether a potential participant meets all selection criteria. In case of questions about whether a participant meets all criteria on medical grounds (e.g. presence or absence of chronic disease), study staff will confer with health center staff, and where appropriate with the potential participant, to reach a final decision on whether to offer enrollment.

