***(End Uganda site-specific information.)***

Those women who are screened and found to be ineligible for the study on medical grounds (i.e. selection criteria 6-9 and 11) will be managed according to routine practice by health center staff. At each site, HIV counseling and testing is linked to an established treatment program to reduce mother-to-child HIV transmission. Other acute or chronic conditions are managed on-site as capacity allows, or referred to a higher level of the health care system according to local guidelines.

***Uganda site-specific information (as requested by WHO; italic font):*** *As a matter of routine, information pertaining to the age, gestational status, HIV status, and medical and obstetric history is obtained by health center staff during typical antenatal visits at TDH. In particular, as a matter of routine and Uganda national policy, all antenatal attendees are invited to undergo HIV testing. If a potential participant declines routine HIV testing, she will no longer be eligible for the study; she will be so informed, she will not participate in any further study activities, and she will continue with the usual care available at TDH. If a participant agrees to the routine HIV testing and tests negative, she will continue with routine care at TDH and with study activities as described below. If a participant agrees to the routine HIV testing and tests positive, she will no longer be eligible for the study; she will be so informed, she will not participate in any further study activities, and she will be referred to local HIV health care providers for appropriate care. HIV care at the TDH site is typically provided through The Aids Support Organization (TASO), a well-established service which provides counseling, advice and materials for prevention of mother-to-child transmission, prophylaxis of opportunistic infections according to national guidelines, antiretroviral therapy according to national guidelines, and other appropriate services.*

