**17 ETHICAL CONSIDERATIONS AND PARTICIPANT CONFIDENTIALITY**

Ethical approval will be sought from the WHO and from national/institutional review committees in all participating countries. Written informed consent will be obtained from all participants as described in section 7.2. Participants will be identified by coded study numbers rather than names in all data collection forms and electronic databases. No individual identities will be used in any reports or publications resulting from the study. Only study staff and study investigators will have access to the information collected, for purposes of data entry and analysis. At the time of informed consent for study participation, participants will be informed that participation in a research study may involve a loss of privacy; however, for this study no sensitive information will be collected, and only study personnel will have access to the information collected.

REFERENCES

**2.** WHO/AFRO. *A strategic framework for malaria prevention and control during pregnancy in the African region.* Brazzaville: World Health Organization, Regional Office for Africa; 2004. AFR/MAL/O4/01.

**3.** Desai M, ter Kuile FO, Nosten F, et al. Epidemiology and burden of malaria in pregnancy. *Lancet Infect Dis.* Feb 2007;7(2):93-104.

**5.** Rogerson SJ, van den Broek NR, Chaluluka E, Qongwane C, Mhango CG, Molyneux ME. Malaria and anemia in antenatal women in Blantyre, Malawi: a twelve-month survey. *Am J Trop Med Hyg.* Mar 2000;62(3):335-340.

**7.** ter Kuile FO, Parise ME, Verhoeff FH, et al. The burden of co-infection with human immunodeficiency virus type 1 and malaria in pregnant women in sub-saharan Africa. *Am J Trop Med Hyg.* Aug 2004;71(2 Suppl):41-54.

**8.** Brabin BJ. An analysis of malaria in pregnancy in Africa. *Bull World Health Organ.* 1983;61(6):1005-1016.

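### The assurance that no sensitive information is collected contradicts a design that screens on HIV status and obstetric history, and post-consent removal in Uganda leaves a social risk unacknowledged

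*Protocol*

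**What the plan says.** Protocol section 8.1 (Potential risks) states that "no sensitive information will be collected, and no social risks are foreseen for participating women". It then lists the confidentiality safeguards: coded study numbers, locked cabinets and password-protected files.

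Section 17, describing the consent discussion, says that "participants will be informed that participation in a research study may involve a loss of privacy". The same sentence goes on: "for this study no sensitive information will be collected, and only study personnel will have access to the information collected".

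Section 6, criterion 6, requires "Absence of HIV infection", and criterion 7 excludes on past or current obstetrical complications. Section 7.2.1 says that facts on health, obstetric history and HIV "are collected by health center staff as part of routine antenatal care", and that study staff rely on the clinic's "diagnosis of these conditions in determining whether a potential participant meets all selection criteria".

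On timing, the general text of 7.2.1 says: "Study staff will conduct screening interviews with each potential participant after she has completed her antenatal visit for that day". The Uganda text in the same section has the woman sign the consent form and then continue her antenatal visit, with routine HIV testing following. It adds: "If a participant agrees to the routine HIV testing and tests positive, she will no longer be eligible for the study". A woman who declines the test is also removed.

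**The concern.** A risk section and a consent discussion should describe the information that the study actually uses. HIV status and obstetric history are sensitive on any ordinary reading, and here both decide who may take part. If women are told that nothing sensitive is collected, the reassurance weakens the privacy warning that precedes it in the same sentence.

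The Uganda sequence adds a second issue. A woman can be known to have agreed to join and then be removed the same day, after a visit that includes an HIV test. People around her may draw conclusions. The listed safeguards protect stored records, not what others observe. At stake are the accuracy of the stated risk and the quality of consent, not the statistical results.

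**Working it through.** The protocol gives no figure to reproduce on this point. The check is a comparison of sections, followed by one illustrative calculation.

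**1. Is sensitive information used or collected?**
- HIV status: excluded under section 6, criterion 6. Section 7.2.1 has study staff rely on the clinic's diagnosis. The Uganda text has them confer with the woman and the clinician to confirm every criterion. Study staff therefore know that each enrolled woman is HIV-negative and can learn why another was excluded.
- Obstetric history: excluded under criterion 7 and handled in the same way.
- Outcomes: section 7.6.8 collects obstetrical complications and fetal or maternal death. Section 7.5 asks for particular care when data are gathered after a poor birth outcome, so the protocol itself treats these data as sensitive.

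The assurance in 8.1 and 17 is wrong on the protocol's own terms.

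**2. Who is told what?**
- Section 17 places the assurance about sensitive information in the consent discussion. It also includes the warning about loss of privacy, and it does not mention social risk.
- Section 8.1 is the only place that mentions social risk. It is protocol text and says that none are foreseen.

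**3. What is the order of steps in Uganda?**
- Reception checks pregnancy and age, and consent is then discussed in private and signed.
- The visit continues with routine HIV testing. A positive or declined test ends participation.
- Study staff confirm the remaining criteria after the visit, and then hemoglobin.
- Section 7.2.2 ties consent to the time of enrollment and has a study staff member conduct both the screening interview and the consent discussion. Under the general text of 7.2.1, that interview follows the visit.

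Screening is completed after the visit in both descriptions. Only the signature comes earlier in Uganda, and the sections do not agree on when consent is taken.

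**4. Can removal reveal HIV status?**
After consent a woman can also be removed for drug reactions, obstetrical history, chronic disease, severe acute illness, low hemoglobin or declining the HIV test. Removal therefore permits suspicion but does not establish status. The most concrete case is in 7.2.2 (Uganda): when a 16- or 17-year-old comes with a parent or guardian figure, who may be a husband, that adult co-signs and can then learn that she was found ineligible.

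**5. How many women?**
Let p be the share of consenting women who test HIV-positive, which the protocol does not give. If the 345 women enrolled in Uganda (section 11.3) are those left after HIV exclusions only, the number removed for a positive result is 345 × p / (1 − p).
- p = 0.03 (assumed): 345 × 0.03 / 0.97 = 10.7
- p = 0.10 (assumed): 345 × 0.10 / 0.90 = 38.3

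These are removals, not disclosures. The protocol gives no rate at which removal leads anyone to infer HIV status, and no count of minors with a co-signing adult.

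**The case against.** The strongest defence is that HIV testing and history-taking are routine care by health center staff, HIV status is not in the analysis data set of section 11.2, and women who complete enrollment are HIV-negative by criterion 6. On that view the study collects nothing sensitive from its participants. This does not rescue the sentence. The study obtains the HIV result through the clinic and acts on it. The Uganda text calls a woman a participant before her result is known. Obstetrical complications and deaths are collected directly.

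Other parts of the defence do stand, and they limit the point. A reader might infer four stronger claims:
- **That women are told there is no social risk.** The documents do not show this. That wording is in 8.1 only, and the consent form is not in the review copy.
- **That removal discloses HIV status, or that a co-signing adult sees the result.** It does not. Removal has many causes, the adult sees ineligibility only, and consent is discussed in private.
- **That Uganda reverses the screening order.** Eligibility is still confirmed after the visit.
- **That Uganda consent should move to after HIV testing.** This is not clearly better. HIV-positive women would either still sign and be dropped, or be visibly not invited. Under section 7.3.3 the RDT results also decide which medicine is given at that visit, so study testing must come before dosing.

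**Conclusion.** The point holds as an internal contradiction in the description of risk. The assurance about sensitive information is wrong as written in 8.1 and 17, and section 17 puts it to women at every site. The statement that no social risks are foreseen does not fit the Uganda sequence, in which removal after consent could lead others to suspect HIV infection and none of the listed safeguards applies.

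The contradiction rests on the text alone and needs no assumption. The range of about 11 to 38 removals depends on an assumed 3% to 10% HIV positivity and ignores all other exclusions, so it only indicates scale. No effect on endpoints, sample size or analysis is shown. The correction is worth making because it is cheap and improves participant protection.

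**What to change.** 1. In 8.1, 17 and the consent discussion, replace the assurance about sensitive information and the sentence on social risk. State instead that HIV status and obstetric history are used to decide eligibility, that sensitive pregnancy outcomes are collected, and that exclusion after consent could lead others to suspect HIV status. Keep the existing warning about loss of privacy.
2. Give every woman found ineligible after consent the same non-specific message, whatever the reason and including in front of any accompanying adult. Discuss the reason only with her, in private.
3. Reconcile the timing of consent between the general text of 7.2.1, the Uganda paragraph and 7.2.2. This need not place Uganda consent after HIV testing.

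Reasons for exclusion can still be recorded; reducing them to a single category would lose information and is not needed here. The cost is amended wording, a short script and staff briefing, and approval of the revised consent text by the review boards. Visits, samples, data items and enrollment targets do not change.
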